### Study endpoints

The primary endpoint is the effect of oral vitamin D at 5,000 and 10,000 IU/day compared with placebo on the frequency of CD4 T-cell subsets and cytokine responses in peripheral blood mononuclear cells in patients with CIS and in healthy control participants at weeks 16 and 24 compared with baseline.

Secondary endpoints include: the following. 1) In the patients with CIS having MRI brain scans at baseline and week 24, the number of new and enlarging T2 lesions and gadolinium-enhancing lesions at week 24 compared with baseline in patients receiving oral vitamin D at 5000 IU and 10,000 IU/ day compared with placebo, 2) In the patients with CIS, the effects of oral vitamin D at 5,000 and 10,000 IU/day compared with placebo on relapse occurrence, calculated as the annualized relapse rate (ARR), the percentage of patients who are relapse-free, and time to first relapse. 3) The effects of oral vitamin D at 5,000 and 10,000 IU/day compared with placebo on the percentage of treated patients with CIS who are free from any evidence of disease (clinical and MRI) activity.

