Immunologic analysis will be carried out at baseline, and at weeks 16 and 24. Peripheral blood mononuclear cells (PBMCs) will be isolated within 12 hours of drawing blood, and cryopreserved until samples from all three time points have been collected. Cytokine production will be measured by ELISA, and will include 1) cytokine production by T cells and by other cells such as monocytes, and 2) flow cytometry, gating specifically on CD4 and CD8 T cells. 1) For analysis of PBMC cytokine production, PBMCs from each timepoint will be thawed out and stimulated with antigen (purified protein derivative (PPD) and tetanus toxoid) or polyclonal stimuli (anti-CD3 and phytohaemaglutinin). After 3 to 5 days (for polyclonal or antigen-specific stimulation respectively), the cell culture supernatants will be assayed by ELISA for cytokines including interleukin (IL)-10 and IL-17, and interferon (IFN)-γ. 1) For flow cytometry analysis of T-cell subsets, stimulated PBMCs from experiment 1, will be re-stimulated on day 5 with PMA and ionomycin in the presence of brefeldin A for 5 hours, followed by cell surface staining for T-cell markers (CD3, CD8) and intracellular staining for cytokines including IL-10, IL-17, and IFN-γ. The cells will be acquired on a FACSCanto II flow cytometer (Becton Dickinson), and analyzed using FlowJo software. Cytokine production by CD3+ CD8− (CD4 T-cells) and CD3+ CD8+ (CD8 T-cells) will be analyzed.

### *MRI scanning* at baseline visit and week 24

Brain MRI will be performed with contiguous axial 3 mm thick slices. Sequences will include axial and coronal T1-weighted spin echo (before and after gadolinium contrast enhancement), axial and sagittal PD/T2-weighted, and axial fast fluid attenuated inversion recovery, before contrast. MRI assessment will include 1) number of gadolinium enhancing lesions, 2) number of new and enlarging T2 lesions, and 3) the total number of new lesions (the sum of 1) and 2)).

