### Sample size

The power calculations for this study were based on a pilot study, which examined immunologic outcomes in four healthy control participants treated with vitamin D 5,000 to 10,000 IU/day at our institution [32]. All calculations for numbers needed in the study were based on α = 5% and β = 80%. Based on flow cytometry analysis of T-cell subsets, the change in IL-17-producing CD4 T-cells (Th17 cells) had an effect size (mean ± SD) of 1.9 ± 1.8 indicating a need for five study subjects per group for 80% power. For IFN-γ-producing CD4 T-cells (Th1 cells), the effect size was 4.3 ± 6.3) indicating a need for 19 subjects per group for 80% power. The changes noted in cytokines in response to anti-CD3 stimulation of PBMC were 1) for IL-17, Δ = 44.5 ± 44.3, thus 10 participants needed in each group; 2) for IFN-γ, Δ = 32.8 ± 1.2, thus 6 needed in each group; and 3) for IL-10, Δ = −455 ± 27, thus number needed is < 5. The changes noted in cytokines in response to PPD stimulation were 1) for IFN-γ, Δ = 1860 ± 1835, thus 10 needed, in each group and 2) for IL-10, Δ = −576 ± 86, thus number needed is <5. On the basis of these results, at least 10 subjects should be included in each group (the only immunologic endpoint not powered would be the flow cytometry analysis of the IFN-γ-producing cells). Recruiting 39 healthy controls and 45 patients with CIS will allow for a drop-out rate of 20% and 30% respectively.

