### Statistical methods

All analyses assume a two-sided test of hypothesis with an overall α level of 0.05. Immunologic endpoints and *post hoc* analyses, which will include the 16 and 24 week endpoints, are considered exploratory, and will not be adjusted for multiple comparisons. Descriptive statistics will be presented as mean ± SD. Non-parametric tests will be used to compare characteristics between treatment groups. For outcomes, the sign/sign rank test will be used to evaluate continuous outcomes. McNemar testing will be used to categorize categorical and binary outcomes. For non-parametric testing on unpaired continuous data, the Wilcoxon rank sum test will be used. All outcomes will be adjusted for baseline serum 25(OH)D levels, and for mean serum levels achieved at weeks 16 and 24.

Missing data will be imputed as the mean of the preceding and following measurements. Only patients completing at least 4 months of full participation in the study or experiencing a relapse at any time in the study will be included in the final analysis. Non-adherent participants, defined as those with an increase in serum level of 25(OH)D of less than 50 nmol/l from baseline, will be excluded from the final analysis.

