## Discussion

Supplemental vitamin D appears to have potential as a therapeutic agent for MS; what is less clear is the optimal dose of vitamin D needed to effect change within the immune system. Our study is designed to address this question, and to add to the growing evidence of the safety and tolerability of high-dose vitamin D supplementation. As this is a phase II randomized, placebo-controlled trial with two distinct study groups and is adequately powered to meet the primary endpoint, it should be considered a high-quality trial aiming to provide class II evidence of the primary endpoint.

Existing guidelines on vitamin D supplementation are conservative, and refer mainly to bone health [33], with 4,000 IU considered the upper limit of tolerability, despite the fact that sun exposure can provide an adult with up to 20,000 IU per day [34]. Older adults are now advised to sustain 25(OH) D concentrations of greater than 75 nmol/l for optimal bone health and, in order to achieve that, they need to consume approximately 4,000 IU/day of vitamin D [18,35]. Levels greater than 100 nmol/l are needed to ensure that patients are receiving adequate immunomodulating doses of vitamin D. Based on previous dosing studies [18], the maximum serum 25(OH)D level expected with a daily dose of 10,000 IU is approximately 250 nmol/l, making both treatment doses safe and tolerable.

The availability of DMT and the earlier recognition and diagnosis of MS have a significant effect on trial design for the evaluation of new drugs, and this also raises ethical concerns. Most would feel that placebo-controlled studies of the RRMS population are unethical. This results in the need for large multicenter trials to achieve adequate numbers to power the study over longer time periods to assess for clinical endpoints. Thus, costs are generally prohibitive and really limits these studies to large pharmaceutical companies.

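### The Discussion claims adequate power for the primary endpoint without exception, although the Sample size section concedes that one of its components, Th1 frequency, is not powered

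*Protocol article*

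**What the plan says.** **Study endpoints** contrasts each vitamin D dose with placebo. The primary endpoint is the effect "on the frequency of CD4 T-cell subsets and cytokine responses in peripheral blood mononuclear cells in patients with CIS and in healthy control participants". Change is assessed from baseline to week 16 and to week 24.

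**Sample size** gives the Th1 input: "For IFN-γ-producing CD4 T-cells (Th1 cells), the effect size was 4.3 ± 6.3". From this it derives the requirement, "indicating a need for 19 subjects per group for 80% power". It then settles on no fewer than 10 per group and adds that "the only immunologic endpoint not powered would be the flow cytometry analysis of the IFN-γ-producing cells". The effects come from a pilot in four treated healthy controls. Enrollment of 39 controls and 45 patients with CIS is said to allow for 20% and 30% drop-out.

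**Randomization** allocates the two cohorts separately, in equal numbers to three arms.

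**Discussion** states that the trial "is adequately powered to meet the primary endpoint", with no exception, and relies on this when it describes the trial as high quality and aiming at class II evidence.

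**The concern.** Th1 frequency is a CD4 T-cell subset frequency, so it is part of the primary endpoint as defined. One section says this component is not powered; another says the primary endpoint is adequately powered. Both cannot stand.

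What is at stake is how a negative result is read. Someone who relies on the Discussion could take a null Th1 finding as evidence of no effect from a trial sized to detect one. On the protocol's own inputs, a true Th1 change of the assumed size would be missed about half the time at the planned number of evaluable participants, even on the more favorable within-group basis.

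**Working it through.** **Inputs**
- Th1 change 4.3, SD 6.3 (Sample size).
- α = 5% and 80% power. The protocol prints "All calculations for numbers needed in the study were based on α = 5% and β = 80"%, which is read here as power of 80%.
- Two-sided testing: "All analyses assume a two-sided test of hypothesis with an overall α level of 0.05" (Statistical methods).
- Enrolled per arm: 39/3 = 13 controls; 45/3 = 15 patients with CIS.
- Evaluable per arm after the stated drop-out: 13 × 0.8 = 10.4; 15 × 0.7 = 10.5. This matches the planned minimum of 10.

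**Step 1: reproduce the 19.** Standardized effect d = 4.3/6.3 = 0.683. For a paired (one-sample) t-test, power comes from the noncentral t distribution with n − 1 degrees of freedom and noncentrality d√n. The smallest n reaching 80% is 19 (power 80.3%), exactly as printed. A paired normal approximation gives 16.85, so 17. A two-sample t-test gives 35 per arm. The printed figure therefore matches a within-group change, not a comparison with placebo.

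**Step 2: Th1 power at the numbers the trial can have.** The two-sample column uses noncentrality d√(n/2) with 2n − 2 degrees of freedom, and assumes that 4.3 is the difference in change between arms and 6.3 the SD in each arm.

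| n per arm | Situation | d√n | Paired t | Two-sample t against placebo |
|---|---|---|---|---|
| 10 | planned evaluable | 2.16 | 49% | 30% |
| 13 | all controls retained | 2.46 | 62% | 39% |
| 15 | all patients with CIS retained | 2.64 | 69% | 44% |
| 19 | stated need | 2.98 | 80% | 54% |

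Both 13 and 15 are below 19, so the stated need cannot be met in either cohort.

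**Step 3: can the other sized readouts simply be called powered?** The calculations cover seven readouts: Th17; Th1; IL-17, IFN-γ and IL-10 after anti-CD3; IFN-γ and IL-10 after PPD. On the two-sample basis of Step 2, at 10 per arm:
- Th17 (d = 1.9/1.8 = 1.056): 61%
- IL-17 after anti-CD3 (d = 44.5/44.3 = 1.005): 57%
- IFN-γ after PPD (d = 1860/1835 = 1.014): 57%

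The other three have printed SDs so small relative to the change that 2 or 3 per arm would suffice arithmetically. The Sample size section presents no placebo comparison for any of the seven. A reworded Discussion sentence therefore should not describe the remaining six as powered for the comparison with placebo.

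**The case against.** **The gap is disclosed and the trial is exploratory.** The Sample size section prints the 19 and names Th1 as the exception. The title, Trial design and Statistical methods all use the word exploratory. The Discussion sentence sets no sample size, analysis or decision rule. All of this stands and limits the weight of the point. It would excuse low power, but not a claim of adequate power. That a null Th1 result will be misread is a risk, not something the protocol prescribes.

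**The paired t-test is inferred.** The Sample size section names no test, and Statistical methods lists sign, signed rank and rank sum tests. The paired t-test returns the printed 19 and both printed 10s, but gives 10 where Th17 is printed as 5, and 2 where IFN-γ after anti-CD3 is printed as 6. This stands as a caveat on the exact percentages. The contradiction does not depend on it, because the protocol itself states the 19 and the shortfall.

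**The cohorts could be pooled.** About 20 evaluable per arm would give 83% on the paired basis, but only 56% against placebo. The protocol randomizes the cohorts separately, gives each its own drop-out allowance and states no pooled power calculation.

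**A stronger reading that the document does not support.** The assays use cells "stimulated with antigen (purified protein derivative (PPD) and tetanus toxoid) or polyclonal stimuli (anti-CD3 and phytohaemaglutinin". No calculation is given for tetanus toxoid, phytohaemagglutinin, IL-17 after PPD, or IL-10-producing CD4 T-cells. A reader might infer that calling Th1 the sole unpowered endpoint is false, and count the unsized readouts. But that remark is introduced as following from the results just listed, and reads naturally as covering those seven. Among them, Th1 is the only one whose stated need exceeds 10. The cytokine list is open-ended and the article does not say every cytokine is read under every stimulus, so any count would be the reader's own construction. A condensed article may also size on selected readouts. What remains is that the sentence could state its scope more clearly.

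**Conclusion.** The point holds as an overstatement in the Discussion: it claims power for the whole primary endpoint that the Sample size section says the design lacks for Th1 frequency. The figure of 19 is not itself an arithmetic error.

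Against the 80% standard, Th1 power is 49% at the planned 10 per group and at most 69% with complete retention, reading 6.3 as the SD of within-person change and using a two-sided paired t-test. For the comparison that the endpoint actually specifies, it is about 30% at 10 per arm; this assumes the same effect and SD carry over to each arm, which the document does not say. All figures take pilot estimates from four people at face value. The Sample size sentence about Th1 being the only exception needs its scope stated; it is not shown to be wrong for the readouts it follows.

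**What to change.** 1. **Discussion:** remove the unqualified power claim. Alternatively, carry over the Th1 exception and state that the calculations cover only the seven readouts listed under Sample size and rest on within-group change. Do not describe the other six as powered for the comparison with placebo.
2. **Sample size:** limit the remark that Th1 is the only endpoint not powered by adding words such as *of the readouts sized above*.
3. **Reporting:** present null Th1 results as inconclusive, with confidence intervals.

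The cost is two reworded sentences, a reporting commitment and a less favorable power statement. Enrollment and assays do not change.

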## Trial status

This trial is active and has been recruiting from November 2012.

## Abbreviations

ARR: Annualized relapse rate; CIS: Clinically isolated syndrome; DMT: Disease-modifying therapy; MRI: Magnetic resonance imaging; MS: Multiple sclerosis; PBMC: Peripheral blood mononuclear cells; RCT: Randomized control trial; RRMS: Relapsing remitting multiple sclerosis; VDR: Vitamin D receptor.
